# SUMMARY OF PROTOCOL CHANGES

Changes to the protocol since version 1.0 are summarized in the following table

| Number | Date | Type | Brief Details |
| --- | --- | --- | --- |
| 1 | 09/01/2020 | General Information | Inclusion of clinical site Co-Is |
| 2 | 09/01/2020 | Study Design | Simplify to two arm trial of intervention vs control |
| 3 | 20/01/2021 | Study Design | Pragmatic study design: eligibility criteria, sample size |
| 4 | 06/05/2021 | General Information;  Study Design | Inclusion of new clinical site Co-I;  Original three arm trial plus pragmatic study design; modified eligibility criteria |
| 5 | 06/09/2022 | Study Design | Adding recruitment sites |

# Background Information

Chronic non-communicable diseases such as diabetes mellitus are a major health expense for Hong Kong, and the rest of China. In Hong Kong and China, the prevalence of type 2 diabetes among the adults has exceeded 10% ^1^. Worryingly, this epidemic is projected to grow as over 35% of adults in China (388 million) have pre-diabetes ^2^. Modifiable lifestyle choices contribute to the growing epidemic of type 2 diabetes. Over 56% of adults in Hong Kong do not meet the World Health Organization recommendations for physical activity and over 79% consume less than the recommended five daily servings of fruit and vegetables ^3^. The first management step for a person with newly diagnosed type 2 diabetes is to adopt an intensive behavioural lifestyle intervention programme of healthy diet, physical activity and smoking cessation. This recommendation is consistent among clinical best practice guidelines in Hong Kong, UK and USA ^4–6^.

Insights from behavioural economics are promising ways for encouraging behaviour change. Increasingly employers and insurers are introducing behavioural incentives in health promotion programs to increase healthy choices such as physical activity ^7^. A number of techniques from behavioural economics could be leveraged in designing incentives ^8,9^. For example, individuals are more motivated by framing rewards as losses rather than gains; this loss aversion can be incorporated in the incentives by offering payment upfront with money taken away if targets are not met. Frequent individualised feedback with appropriate framing of the incentive could be used to reinforce the new behaviour. Non-financial techniques can also be leveraged such as feedback of performance relative to peers (rank/percentile), social influence, priming and gamification.

A recent review found a small number of trials of behavioural economic-based incentives on healthy behaviours such as weight loss, physical activity, and medication adherence ^10^. There is a lack of trials that measured clinical indicators such as glycaemic control (HbA1c), that are strong predictive of diabetes complications ^5^. Incentives based on behavioural economics have improved adherence to chronic disease management but have not been used at the early stages of diseases, where there lies an opportunity to delay or reverse the onset of diabetes. Developing new habits may be best facilitated by presenting incentives at moments when an individual is most likely to act, such as being informed of a new diagnosis of chronic disease. No trials have been conducted among the Chinese population with different cultural and social norms to risk compared to Western-settings, despite Chinese respondents being more risk-seeking than Americans ^11^.

# Aims and Objectives

The aim of this study is to test the effectiveness of incentives that use insights from behavioural economics to promote diabetes control and healthy behaviours among people newly diagnosed with type 2 diabetes.

## Primary objective

- To investigate the effect of financial and social incentives based on behavioural economic principles on glycaemic control at 6-months for people with newly diagnosed type 2 diabetes.

## Secondary objectives

- To examine the sustainability of glycaemic control at 9-months following the withdrawal of incentives for people with newly diagnosed type 2 diabetes.
- To study the effect of incentives based on behavioural economic principles on other health indicators including lipid profile, body weight/BMI, blood pressure, diet, physical activity, smoking, and delay of diabetes for people with newly diagnosed type 2 diabetes.

# Study Design

This study is a randomized controlled trial in adults aged 30-70 (at enrolment) with newly diagnosed type 2 diabetes over the study period of Jan 2020 to Dec 2022. We plan to enrol 261 adults and follow them for 9-months (6-month intervention period and a 3-month post-intervention follow-up period) to assess glycaemic control and other health indicators. A meta-analyses of clinical trials show a pooled difference of -0.6 percentage points in HbA1c after a minimum 8-12 weeks of exercise intervention ^12,13^. Consequently, the 6-month intervention period is designed to be sufficient to assess changes in lifestyle, but not of excess duration in order to reduce participant drop-out and loss to follow-up. If a 6-month trial of lifestyle intervention fails to adequately control blood glucose level, it may be appropriate to consider additional medication for glycaemic control ^4–6^.

Participants will be randomly assigned to one of three groups (in ratio 1:1:1): arm A (financial incentives in addition to standard care), arm B (financial and social incentives in addition to standard care), and arm C (control arm receiving standard care). All participants will establish a baseline step count of physical activity using the second week of recorded measurements. The first week of recorded measurements will be ignored to minimise the potential upward bias from elevated physical activity during initial device use. Subsequently, all participants will receive weekly increases of 1,000 daily step targets from their baseline levels to a maximum target of 10,000 steps per day (depending on age, physical condition, physician guidance). The 10,000-step target approximates the 30 minutes of daily exercise recommended by the American College of Sports Medicine ^14^. We will impute daily values less than 1,000 steps as these values are unlikely to represent actual activity ^15,16^. Participants will use their smartphones to track step counts on the same pre-specified activity tracking app for consistency. Although smartphones are expensive, smartphone penetration in Hong Kong is very high, at above 88% of the population aged 10 or above in 2017 ^17^. All participants will be provided with a pedometer to account for physical activity. Participants are followed for an additional 3-months after the cessation of incentives to assess any continued effects and the sustainability of lifestyle change.

Arm A (financial incentives): Participants will receive the usual standard care (same as control group), a loss-framed financial incentive, and weekly feedback on performance for 6 months.

Arm B (financial and social incentives): Participants will receive the usual standard care (same as control group), a loss-framed financial incentive, social incentives, and weekly feedback on performance for 6 months.

Arm C (control): Participants will receive standard care under the risk factor assessment and management programme (RAMP) including patient screening and education on diet, physical activity, and smoking conducted by a multi-disciplinary team ^18^.

The study will last for a total of 36 months including a 11-month suspension due to COVID-19 pandemic. This includes a 11-month recruitment period on rolling basis, 9-month follow-up period for each participant (consisting of 6-months intervention period and 3-month post-intervention period) and 3-month buffer for any rescheduling of follow-up. We plan to allow 4-months for the data analysis and 3-months to write-up our findings.

The pragmatic study design is based on the PRECIS-2 tool (Appendix 3) and RE-AIM frameworks.^19,20^ This trial is registered at ClinicalTrials.gov and will follow this pre-specified protocol.

## Participant enrolment

In this study, invitations to participate will be extended to community-dwelling adults in Hong Kong through general outpatient clinics (GOPC) for family medicine & primary care, District Health Centres and supporting organisations. Eligible and interested adults will be identified and invited to join this study during their routine medical appointment at the GOPC. The contact information of the patients will be forwarded to the research staff for screening and study meet-up arrangement. Participants will be screened over phone within one month. The patients will subsequently come to study clinics for enrolment and other trial-related activities.

## Informed consent

Written informed consent will be sought from each eligible adult who is willing to participate in the study – a copy of the consent form will be provided to the patient. We will assess the cognitive function and ability to provide informed consent using a screening tool (Mini-Cog^21^) for all participants age over 60 years.

## Enrolment interview

A short standardized questionnaire will be administered by trained research personnel to collect background information including demographics (age, sex, current job status, education level, monthly household income, smoking status), body weight and height, general functional and health status including breastfeeding (for women), existing medical conditions (chronic cardiovascular, pulmonary, renal, hepatic, metabolic, autoimmune and immunocompromising diseases or treatment), medication use, levels of physical activity, diet, and health-related quality of life.

## Collection of blood samples

Simple blood tests will be given to all participants as an incentive, and we will collect 3-10 mL of blood from each participant at baseline (if no contemporaneous results), 6-months and 9-months for this purpose. Only registered phlebotomist or trained nurses will collect blood samples. Blood specimens will be collected and tested by designated laboratory. Results will be issued by registered medical laboratory technologist.

## Randomization

The random allocation process will be concealed from the front-line team, using tamper-proof methods, by way of pre-assignment based on a computer-generated sequence of random numbers administered by an independent research assistant. A sequence of random numbers will be generated prior to the start of the study by a statistician. To avoid baseline unbalance, we will stratify the randomization by age (30-49, 50-70) and sex. Computer software (R) will be used to generate the randomization sequence, using a block randomization structure with block sizes of 6 for the enrolment of participants.

The study will remain blind to laboratory and analysis staff. Research staff members at the designated study clinics who had no access to the randomization sequence will allocate a unique code to each of the participants based on their order of attendance. Because the allocation process will be concealed, the identity of the intervention groups will be unknown to the laboratory staff. The randomization codes will be masked from those assessing the outcomes and will only be revealed to the investigators after completion of the follow-up. A study statistician, uninvolved with other trial activities, will have access to the randomization codes for the purpose of conducting regular interim analyses and safety monitoring.

We will enrol 261 participants and randomly allocate each participant to one of the three study arms in equal proportion (1:1:1 ratio) (Figure 1). We assume 10% of participants do not complete the intervention or are lost to follow-up.

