Feedback messages will be positively framed and sent weekly to garner encouragement. Participants enrolled in intervention arm A (financial incentives) with their daily step count target met will receive individualized feedback by text message: “Well done and congratulations! You achieved your physical activity goal this week! You have $1,000 remaining in your account.”. The remaining participants in this arm will be told the balance in their account after penalty of losing HKD40: “Sorry, you did not meet your physical activity goal this week. You lost $40 from your account. Remaining balance = $960.”. Participants achieving their daily step-count target in intervention arm B (financial and social incentives) will receive weekly monitoring and individualized feedback during the incentive period by text message: “Well done and congratulations! You achieved your physical activity goal this week! X% of all participants met their targets this week (X% exceeded!). You have $1,000 remaining in your account.”. Those not meeting their targets in this arm will be told they did not meet their targets and the balance in their account after penalty of losing HKD40: “Sorry, you did not meet your physical activity goal this week. X% of all participants met their targets this week (X% exceeded!). You lost $40 from your account. Remaining balance = $960. Keep it up and strive for your best next week!”.

Participants who are not able to record and share their step counts on a weekly basis will receive messages or phone calls from the research team to record their physical activity performance. The incentives are discontinued during the post-intervention follow-up period.

Participants being enrolled in the control arm will not be told their baseline step count after the second week. They will receive the routine care but not weekly feedback nor messages.

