# Assessment of Safety

Participants should report any adverse events to the study co-ordinator (contact details are provided to participants). Given the non-clinical nature of the intervention, we do not anticipate any occurrence of SAEs within our study. We will survey participants for any safety issues at 6-months and 9-months after enrolment. We will record and inform the IRB of any reported adverse events. For stopping rule, refer to section 6.2 for details. All trial-related activities including enrolment and follow-up will be conducted by our delegated research team members from the School of Public Health, the University of Hong Kong.

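### A single stated block size of 6 could make up to about 20% of allocations foreseeable to anyone who knows every earlier assignment in the stratum; randomly varied, undisclosed sizes would remove most of that certainty

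*Protocol*

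**What the plan says.** The Randomization section of the protocol gives the whole scheme. There are 261 participants and three arms in equal ratio. On strata it says "we will stratify the randomization by age (30-49, 50-70) and sex", which makes four; site is not a stratum. On blocks it says "using a block randomization structure with block sizes of 6 for the enrolment of participants". No second size and no random variation of size is mentioned.

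The same section protects the list itself: "The random allocation process will be concealed from the front-line team, using tamper-proof methods". An independent research assistant administers it. Codes are given in order of attendance: "Research staff members at the designated study clinics who had no access to the randomization sequence will allocate a unique code". Masking is stated for laboratory staff, analysis staff and outcome assessors, and the investigators receive the codes only after follow-up.

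Under Interventions to be Administered, arms A and B have a credited account and weekly texts whose content differs between the two arms. Of the control participants it says "They will receive the routine care but not weekly feedback nor messages". Assessment of Safety adds "All trial-related activities including enrolment and follow-up will be conducted by our delegated research team members".

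**The concern.** Concealing a list stops staff from looking up the next allocation. It does not stop them from working it out by counting, if they know the block size and can see what has already been assigned. Here the size is constant and printed. The arms differ visibly after assignment, so the trial is open-label in effect, though the protocol does not use that term. One delegated team covers enrolment and follow-up, and no sentence keeps its enrolling members unaware of earlier assignments.

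Prediction matters only if someone can act on it. Under Participant enrolment, research staff receive patients' contact details for screening and for arranging the study visit, and codes follow order of attendance. Staff who arrange visits could therefore influence who comes next, and the stratifiers, age and sex, are easily known beforehand. If more motivated patients were steered towards or away from the incentive arms, the HbA1c comparison could be biased. The baseline covariate in Statistical methods would not remove this, because motivation is not in the model.

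**Working it through.** The protocol gives no predictability figure, so there is none to reproduce.

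**Inputs (Protocol, Randomization):** block size 6; three arms at 1:1:1, hence 2 + 2 + 2 per block; 261 participants; four strata. A block has 6!/(2!·2!·2!) = 90 equally likely orders.

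**Full knowledge of earlier assignments in the stratum.** Probability by position in the block:

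| Position | Arm certain | At least one arm used up | Incentive versus control certain | Best guess of arm right |
|---|---|---|---|---|
| 1 | 0 | 0 | 0 | 1/3 |
| 2 | 0 | 0 | 0 | 2/5 |
| 3 | 0 | 1/5 | 1/15 | 1/2 |
| 4 | 0 | 3/5 | 3/15 | 8/15 |
| 5 | 1/5 | 1 | 7/15 | 3/5 |
| 6 | 1 | 1 | 1 | 1 |
| Sum | 1.2 | 2.8 | 26/15 | 3.367 |
| Sum ÷ 6 | **20.0%** | **46.7%** | **28.9%** | **56.1%** |

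The arm at position 5 is certain only when the last two slots hold the same arm, which has probability 1/5. Control status is known when both control slots are used or only control slots remain. A best guess by chance would be right 33% of the time.

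Simulating 261 participants in four strata with incomplete last blocks gave about 50 certain allocations, or 19%. The result was nearly the same for three assumed splits of stratum sizes.

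**Incomplete knowledge.**

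- Only the latest assignment in the stratum is unknown. Position 5 is never certain, because three slots remain open and no arm has three. Position 6 is certain with probability 1/5. Share: 0.2/6 = 3.3%.
- The latest two are unknown. Three slots are open even at position 6, so the share is 0%.
- Each earlier assignment is known independently with an assumed probability of 75%, 50% or 33%. Simulated share: about 6%, 1.2% or 0.2%.

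**After the change.** Two simulations used sizes 6, 9 and 12 in random order and an observer who knows that set but not the order.

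- Certain allocations: 2.5% and 2.8%.
- Best guess right: 52.1% and 52.8%.
- Fixed blocks of 6, in the first of these simulations (65 per stratum): 18.9% certain and 55.4% right.

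A larger fixed block is not enough: size 9 still leaves 1/7 = 14.3% certain.

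**The case against.** The strongest reply is that the 20% describes an observer the protocol does not describe. The list is concealed, an independent assistant runs it, and clinic staff who give codes cannot see it. The section on interventions does not say who sends the weekly texts or keeps the accounts; it names the research team only for chasing participants who do not share step counts. A delegated team can have divided roles. Recruitment runs through several sources, and the strata are not split by site, so staff at one clinic may miss assignments made elsewhere. As shown above, one missing assignment is enough to cut the figure to 3.3%.

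The texts are also a slow signal. With 261 participants over the 11-month recruitment period and equal strata assumed, a stratum enrols 261/11/4 = 5.9 a month, or one about every five days. Target-based feedback can start only after the week-2 baseline, by which time roughly three or four more people have entered the stratum. On that average pace the texts alone would give no certain allocations; faster knowledge would have to come from the credited accounts or from participants. A forecast made when a visit is booked may also be out of date by the visit. Finally, entry is limited to HbA1c of 6.5–9% and baseline is a covariate, which limits steering on disease severity.

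All of this stands as a limit on size. It does not justify a single printed block size, because the protocol does not exclude the knowledge that makes prediction possible, and neither the entry range nor the covariate addresses motivation.

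**Conclusion.** The point holds as a cheap improvement to the allocation scheme. A fixed, stated block size of 6 leaves up to about 20% of allocations certain, and incentive versus control certain for about 29%, for someone who knows the size and all earlier assignments in the stratum. With less knowledge the share is far lower: 3.3% without the latest assignment, and about 6% or 1% under the assumed 75% or 50% knowledge. Concealment of the list may therefore not fully prevent selection bias.

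A reader might infer three stronger statements that the protocol does not support:

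- **That enrolling staff will in fact foresee a fifth of allocations.** The protocol does not say that they learn earlier assignments.
- **That the people who enrol also send the texts and run the accounts.** A shared delegated team makes this possible, but it is not stated.
- **That the HbA1c comparison is biased.** Predictability is an opportunity for bias, and no effect on HbA1c has been estimated.

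**What to change.** For the sequence, or any part of it not yet allocated, generate blocks in R with randomly varied sizes that are multiples of three, for example 6, 9 and 12, within the same four strata. In the Randomization section, replace the stated size of 6 with: *randomly varied block sizes, not disclosed to enrolling staff*. Keep the sizes in a restricted file. A further sentence saying that enrolling staff are kept unaware of earlier assignments would complement this.

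The gain is in certainty, since best-guess accuracy hardly changes. The costs are a small code change, one protocol sentence and slightly larger possible imbalance from incomplete last blocks. The sequence was to be generated before the start of the study, and the latest listed protocol change is dated September 2022 in a study period ending December 2022. If recruitment has begun, the unused part of a live list must be replaced, which is more work than a code edit. Nothing can be gained for participants already allocated.

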**Figure 1. CONSORT Flow Diagram**

Discontinued or Lost to follow-up (n=13)

Analysed (n=74)

Analysed (n=74)

**Analysis**

Analysed (n=74)

Discontinued or Lost to follow-up (n=13)

Discontinued or Lost to follow-up (n=13)

**Follow-Up**

**Allocation**

**Arm A: Financial incentives**

- Received allocated control (n=87)

**Arm B: Financial and social incentives**

- Received allocated intervention (n=87)

**Arm C: Control**

- Received allocated intervention (n=87)

**Enrolment**

Assessed for eligibility (n=301)

Excluded (n=40)

- Not meeting inclusion criteria
- Declined to participate
- Other reasons

Randomized (n=261)

## Follow-up assessments

A follow-up assessment on health information, similar to the baseline enrolment questionnaire, including body weight and height, general health, medication usage and health service usage will be collected when participants have blood drawn 6 months after enrolment. In usual practice, newly diagnosed patients with type 2 diabetes attend regular medical appointment every 3 months to monitor their condition. A brief follow-up assessment will be completed at 9 months for all participants to monitor changes in health status of the participants longitudinally.

